##### Descriptive cross-sectional study

1. Males and females 0 to 15 years
2. Presumptive pulmonary or extra-pulmonary TB cases based on clinical symptoms and/or positive AFB smear, culture, or molecular-confirmed disease
3. Patients receiving outpatient TB treatment through Mulago National Referral Hospital or Fort Portal Regional Referral Hospital

#### **Exclusion criteria:**

##### Retrospective study and historic cohort study

1. Age greater than or equal to 15 years
2. The patient was determined not to have TB during the admission
3. Clinical notes irretrievable
4. Meningitis in post-operative setting, post-traumatic meningitis, or parameningeal infections
5. Chronic meningitis other than tuberculous meningitis

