## Abstract:

**Background:** The purpose of this study is to describe disease trends, outcomes, and risk factors for pediatric tuberculosis infection in rural vs urban settings.

**Methods:** To determine disease trends in the number of diagnosed pediatric tuberculosis cases in rural vs urban settings, in Aim 1, we will complete a retrospective study of 100 children, <15 years old, diagnosed with active tuberculosis from January 2016-June 2021 at Mulago National Referral Hospital and Fort Portal Regional Referral Hospital. We hypothesize that the number of diagnosed tuberculosis cases in both rural and urban settings will decrease over time. Using this same population, in Aim 2, we will complete a historic cohort study to determine pediatric tuberculosis outcomes in rural vs urban settings. We hypothesize that length of hospital stay is longer, and mortality is higher among children with tuberculosis in rural compared to the urban hospital settings. Medical records will be reviewed using a standardized chart abstraction protocol. To identify possible risk factors for development tuberculosis infection in children, in Aim 3, we will perform a cross-sectional descriptive study of children with active tuberculosis, obtaining a risk-factor history via a questionnaire at an outpatient tuberculosis clinic.

**Study Utility:** These results will improve our understanding of rural healthcare disparities in Uganda and provide preliminary data for larger studies to address tuberculosis risk factors and predictors of poor tuberculosis treatment outcomes among children.

[figure not shown]

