**Objectives:**

The primary objectives are:

1. To describe the trends of paediatric TB cases identified over a 5-year period among children <15 years of age in rural and urban settings.
2. To describe the TB treatment outcomes among children < 15 years of age admitted with TB disease in rural and urban settings.
3. To identify risk factors that are present in children <15 years of age with active TB in rural and urban settings.

Specific Hypotheses to be Tested:

[figure not shown]

1. The number of diagnosed TB cases initiating therapy in rural and urban settings will decrease over time.
2. Length of hospital stay in days (LOS) for children with TB is longer in the rural setting vs the urban setting.
3. Mortality is higher among children with TB in the rural hospital setting vs the urban hospital setting.

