### **Study Procedures:**

#### Retrospective study and historic cohort study

We will perform a retrospective chart review of electronic and written medical records for 100 children <15 years of age who were diagnosed with TB at either Mulago National Referral Hospital or a Fort Portal Regional Referral Hospital in Uganda. Cases will be included between January 1, 2016 - June 30, 2021. The medical records will be reviewed, and eligibility will be confirmed through the inclusion and exclusion criteria. If the patient is eligible, the abstractor will proceed with a standardized chart abstraction form. If the patient is not eligible, the abstractor will look for an alternative case until the 100-patient sample is reached. Data elements to be extracted include: name, medical record number, date of birth, sex, address, nationality, ethnicity, hospital admission and discharge date, weight, height, diagnosis at admission, clinical symptoms at admission, date of symptoms onset, history of prematurity, birth weight, prior medical problems, BCG vaccination, history of TB contacts, prior history of TB infection, HIV infection status, CD4 count/percentage and viral load in HIV-infected, TB diagnostics (AFB, culture, PPD), radiographic imaging reports, biopsy reports, cerebral spinal fluid labs, major procedures or interventions, TB treatment regimen, treatment adverse reactions, anti-retroviral treatment regimen for HIV-infected, final diagnosis, discharge status, and follow-up recommendations. When available, data from the 12-month follow-up visit will also be abstracted.

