### **Study Statistics:**

#### Retrospective study and historic cohort study

The primary outcome variables are TB active case trends and treatment outcome at the time of hospital discharge. We will assess all available charts of pediatric patients admitted with active TB. Means and standard deviations (SD) for continuous variables, frequency and percentage for categorical variables will be used to summarize all predictor variables and the outcome variables. Comparisons of categorical variables will be made using Chi-square and comparison of continuous variables will be completed using independent t-tests or nonparametric tests depending on normality of distribution.

To test Hypothesis 1, that the number of diagnosed TB cases initiating therapy in rural and urban settings will decrease over time, we will fit a linear regression model with number of monthly cases diagnosed as outcome and study period (in months) as the predictor with the initial month of the study period (01-Jan-2016) represented as "1" and the final month of study period 06-Jun-2021 represented as "66", accepting a linear assumption that cases are evenly distributed across each month. We will further fit an interaction term in this regression model, between dichotomous TB diagnosis location (urban or rural) and continuous study period. In an alternative model, we will test for the bivariate correlation between the annual number of cases diagnosed and the year of diagnosis by computing the Pearson's correlation coefficient, with significant temporal trend defined as a  $p < 0.05$ . To test Hypothesis 2, that length of hospital stay in days (LOS) for children with TBM is longer in rural vs urban settings, we will fit a linear regression model with LOS as continuous outcome and location as dichotomous predictor, controlling for a-prior selected potential confounders. To test Hypothesis 3, that mortality is higher among children with TBM in the rural hospital setting vs the urban hospital setting, we will fit a multivariable logistic regression model with in-hospital mortality as dichotomous outcome and location as dichotomous predictor.

[figure not shown]

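### Exclusion 3 makes the Hypothesis 1 monthly case count depend on chart retrieval, while the trend model treats every month as fully observed

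*Protocol*

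**What the plan says.** Under Exclusion criteria, the Protocol gives one list for the retrospective study (Aim 1) and the historic cohort study (Aim 2). Its third item is "Clinical notes irretrievable".

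Hypothesis 1 under Objectives reads: "The number of diagnosed TB cases initiating therapy in rural and urban settings will decrease over time". Under Study Statistics the case trend is a primary outcome, tested by linear regression with "number of monthly cases diagnosed as outcome and study period (in months) as the predictor". Months run from 1 to 66, and a location-by-month interaction is added. The only statement about completeness is that the authors are "accepting a linear assumption that cases are evenly distributed across each month". No offset, weight or adjustment for missing files is given.

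Three statements bear on where the count comes from:

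- Abstract: "in Aim 1, we will complete a retrospective study of 100 children".
- Study Procedures: "If the patient is not eligible, the abstractor will look for an alternative case until the 100-patient sample is reached".
- Study Statistics: "We will assess all available charts of pediatric patients admitted with active TB".

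The second and third do not agree on whether the count is a sample of 100 or every available chart. Under either, a child whose notes cannot be found is not counted.

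**The concern.** The two aims need different things from a chart. Aim 2 cannot use a child without notes, because stay, discharge status and confounders are in the notes. Aim 1 needs only to know that a case occurred, where, and in which month. One exclusion rule for both removes real cases from the Aim 1 outcome.

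The removal matters if its rate changes over the 66 months or changes differently at the two hospitals. The Protocol expects some loss, since it lists it as an exclusion. It describes records that are partly electronic and partly written, and it budgets a separate records assistant for each hospital. Unequal retrieval is therefore possible, but the Protocol does not say that it occurs.

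At stake are the slope that tests Hypothesis 1 and the interaction that compares rural with urban trends. Either could reflect record keeping rather than tuberculosis. Unless lost files are logged by month and hospital, no later analysis can tell the two apart.

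**Working it through.** **Inputs from the Protocol.** Study period January 2016 to June 2021: 5 × 12 + 6 = 66 months, which agrees with the stated index. Two settings, so 132 setting-months. Planned charts: 100. The significance level of 0.05 is stated for the annual correlation; I take it as two-sided and use it for the regression too. The Protocol gives no figure for retrieval or for power on Hypothesis 1, so there is no figure of its own to reproduce.

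**Assumed inputs.** True counts change linearly by a fraction D from month 1 to month 66. Retrieval changes linearly from r1 to r66.

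**Bias of the slope.** Expected observed count in month m = true count(m) × retrieval(m). The observed end-to-start ratio is (1 − D) × r66 / r1.

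- If r1 = r66, the ratio is 1 − D, so the relative trend is unbiased. Example: 80% throughout and D = 30% gives a fitted -30%.
- The decline is flattened when r1 / r66 = 1 − D and reversed when r1 / r66 is lower. With r66 = 95%, the break-even starting retrieval is 0.95 × 0.90 = 85.5% for D = 10%, 0.95 × 0.80 = 76% for D = 20%, 0.95 × 0.70 = 66.5% for D = 30%, and 0.95 × 0.50 = 47.5% for D = 50%.

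Least-squares fitted change from month 1 to month 66:

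| Retrieval, month 1 to 66 | True change 0% | True -10% | True -30% |
|---|---|---|---|
| 80% throughout | 0% | -10% | -30% |
| 90% to 95% | +6% | -5% | -26% |
| 80% to 95% | +19% | +7% | -17% |
| 70% to 95% | +36% | +22% | -5% |
| 60% to 95% | +58% | +42% | about +10% |
| 95% to 70% | -26% | -34% | -49% |

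The last row shows the opposite pattern, in which recent files are harder to find: a decline is exaggerated, or created where there is none.

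**Effect on the tests** (Poisson counts, ordinary least squares, simulated). These results depend heavily on the caseload, which the Protocol does not state. Two caseloads are shown.

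Probability of a significant decline when the true decline is 30%:

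| Retrieval | One series, 10 cases per month | 100 true cases in all, both hospitals pooled |
|---|---|---|
| Complete | about 68% | about 17% |
| 90% to 95% | about 50% | about 13% |
| 80% to 95% | about 21% | about 7% |
| 70% to 95% | about 5% | about 3% |
| 60% to 95% | about 1% | about 1% |

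False-positive rate of the interaction when both true trends are flat, urban retrieval stays at 95%, and rural retrieval rises to 95%:

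| Rural start | 10 cases per month per hospital | 100 cases in all |
|---|---|---|
| 80% | about 13% | about 6% |
| 70% | about 29% | about 7% |
| 60% | about 50% | about 9% |

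Ten per month per hospital is 10 × 66 × 2 = 1,320 cases. One hundred cases is 100 / 132 = 0.76 per setting-month.

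**The case against.** The strongest objection is that nothing in the Protocol shows that retrieval changes over time. A reader might infer that older files are lost more often, and that the plan will therefore hide or reverse a true decline. The documents do not support this. They give no retrieval rate by year or hospital; constant loss does no harm to the relative trend; a start of 90% only moves -30% to -26%; and the reverse pattern errs the other way. This objection stands against any claim of direction or size. It does not remove the dependence on retrieval, which is written into the exclusion rule.

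Second, the larger test effects need a caseload near 1,320. At the 100 children planned, the false interaction rate stays between about 6% and 9%, and power for a 30% decline is only about 17% with every file present. At that size low counts limit Hypothesis 1 more than retrieval does. This stands.

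Third, the replacement rule is the larger distortion. If abstractors substitute cases until 100 is reached, the monthly numbers reflect which charts were picked, even with no file lost. This also stands, so changing exclusion 3 alone would not be enough.

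Fourth, Hypothesis 1 counts children starting therapy, exclusion 2 removes those found not to have tuberculosis, and the notes are the stated source for both facts. Counting children without notes may admit unconfirmed or untreated ones. Nor does the Protocol describe a register covering both hospitals; the budgeted electronic-record query is not said to be one. These points shape the fix but do not justify leaving the rule as it is.

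Finally, reporting details could be in an analysis plan that is not shown. The exclusion rule is in the Protocol, however, and cases that were never logged cannot be recovered later.

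**Conclusion.** The point holds in conditional form. Exclusion 3 applies to Aim 1, so the Hypothesis 1 count is cases times the share of files found, while the model treats each month as fully observed. Retrieval that changes over time biases the slope, and a pattern that differs by hospital biases the interaction. The sign and size are unknown.

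The illustrative shift of a true 30% decline to -26%, -17%, -5% or about +10% rests on assumed linear retrieval reaching 95%, and does not depend on caseload. The power and false-positive figures do depend on it, and the absolute effects are much smaller at 100 children. The documents do not support a statement that the planned trend will be hidden or reversed. They support saying that, as written, nobody could tell whether it had been. The change is worth making because it is cheap and protects a primary outcome.

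**What to change.** 1. State that exclusion 3 applies to Aim 2 only.
2. State that the replace-until-100 rule serves the Aim 2 chart sample and does not define the Aim 1 count.
3. Log every child identified as a tuberculosis case, with hospital, month, and notes irretrievable yes/no.
4. For Hypothesis 1, fit the trend on all identified cases, including those without notes where the listing or register shows a tuberculosis diagnosis (and treatment start, if recorded). Repeat it on cases with retrieved notes only as a sensitivity analysis. Report the retrieved fraction by hospital and year.
5. Name the listing used at each hospital. If one has none beyond the charts themselves, say so and describe its result as a trend in retrieved charts.

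Dividing each month's count by that month's retrieved fraction is not a good substitute at the planned size: with 0.76 expected cases, about exp(−0.76) = 47% of setting-months contain no case and the fraction is undefined.

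The cost is two sentences in the Protocol and a short screening log. A child can be judged to have irretrievable notes only after being identified somehow, so some source should exist, though its coverage must be checked. The downside is that some listed cases without notes may be unconfirmed or untreated; comparing the two analyses shows how much that matters.

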##### Descriptive cross-sectional study

1. Age greater than or equal to 15 years
2. Unable to contact parent or guardian

### **Study Statistics:**

#### Retrospective study and historic cohort study

The primary outcome variables are TB active case trends and treatment outcome at the time of hospital discharge. We will assess all available charts of pediatric patients admitted with active TB. Means and standard deviations (SD) for continuous variables, frequency and percentage for categorical variables will be used to summarize all predictor variables and the outcome variables. Comparisons of categorical variables will be made using Chi-square and comparison of continuous variables will be completed using independent t-tests or nonparametric tests depending on normality of distribution.

To test Hypothesis 1, that the number of diagnosed TB cases initiating therapy in rural and urban settings will decrease over time, we will fit a linear regression model with number of monthly cases diagnosed as outcome and study period (in months) as the predictor with the initial month of the study period (01-Jan-2016) represented as "1" and the final month of study period 06-Jun-2021 represented as "66", accepting a linear assumption that cases are evenly distributed across each month. We will further fit an interaction term in this regression model, between dichotomous TB diagnosis location (urban or rural) and continuous study period. In an alternative model, we will test for the bivariate correlation between the annual number of cases diagnosed and the year of diagnosis by computing the Pearson's correlation coefficient, with significant temporal trend defined as a  $p < 0.05$ . To test Hypothesis 2, that length of hospital stay in days (LOS) for children with TBM is longer in rural vs urban settings, we will fit a linear regression model with LOS as continuous outcome and location as dichotomous predictor, controlling for a-prior selected potential confounders. To test Hypothesis 3, that mortality is higher among children with TBM in the rural hospital setting vs the urban hospital setting, we will fit a multivariable logistic regression model with in-hospital mortality as dichotomous outcome and location as dichotomous predictor.

[figure not shown]

Sample size calculations to determine the appropriate number of retrospective charts to review are based on Hypothesis 2 using the t-statistic as calculated at [quesgen.com](http://quesgen.com). We will test associations between hospital setting and outcomes (LOS and mortality) in the entire cohort of children with active tuberculosis. Testing our Hypothesis 2,  $n=100$ , we are adequately powered at  $> 80\%$  to detect differences in LOS outcome of  $> 16$  days, an adequate effect size as LOS for children with active TB is typically several weeks (median 36 days, IQR 21-60 days in the (Blount 2014) cohort).

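### Hypothesis 1 claims a fall in cases in both settings, but none of its named tests rests on each setting's own slope, so an urban-only fall could be taken as support for both.

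*Protocol*

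**What the plan says.** The Abstract states the hypothesis for each setting: "We hypothesize that the number of diagnosed tuberculosis cases in both rural and urban settings will decrease over time". The Objectives section repeats it: "The number of diagnosed TB cases initiating therapy in rural and urban settings will decrease over time".

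Study Statistics (Retrospective study and historic cohort study) makes case trend a primary outcome and names three analyses for Hypothesis 1:

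- The main model: "we will fit a linear regression model with number of monthly cases diagnosed as outcome and study period (in months) as the predictor". Month is the only predictor named.
- An extension: "We will further fit an interaction term in this regression model, between dichotomous TB diagnosis location (urban or rural) and continuous study period".
- An alternative: "we will test for the bivariate correlation between the annual number of cases diagnosed and the year of diagnosis by computing the Pearson's correlation coefficient". Its threshold for calling the trend significant is a p-value below 0.05. No split by setting is stated.

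The section does not say that the slope within each setting will be tested, that both must be negative, or how a significant interaction would change the conclusion on Hypothesis 1.

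**The concern.** A claim that cases fall in both settings is false as soon as one setting does not fall. The analysis therefore has to look at each setting separately. A combined slope can be driven by the larger site, and a difference in slopes does not show whether either site is falling.

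The rural setting has most to lose. The Background says that work has been done in Kampala and that rural trends are what remains to be understood. If urban cases fall and rural cases are flat or rising, a significant combined decline could be carried over to the setting the study was set up to describe.

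**Working it through.** **What each analysis tests**

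| Analysis | Null hypothesis | What rejection shows |
|---|---|---|
| Monthly count on month | Combined slope is zero | The total changes; one site is enough |
| Location-by-month term | The two slopes are equal | The trends differ; both, one or neither may fall |
| Annual count with year | No linear association (pooled, on the natural reading) | As the first row |
| Hypothesis 1 as stated | At least one setting does not fall | Cases fall in both |

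None of the first three nulls is the fourth.

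**Inputs.** The period is from the protocol: "Cases will be included between January 1, 2016 - June 30, 2021", which is 5.5 × 12 = 66 months. The criterion is p < 0.05, taken as two-sided because sidedness is not stated. The protocol gives no power figure for Hypothesis 1 (its sample size is for length of stay), so there is no stated figure to reproduce. It gives no monthly volumes or urban-rural split, and refers both to 100 charts and to all available charts. Volumes at two scales are therefore assumed: independent Poisson counts, with the stated starting rate changing linearly over the 66 months.

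**Hand check of the combined slope.** For 66 months, Sxx = 66 × (66² − 1)/12 = 23,952.5. The standard error of a slope is about √(mean monthly count / Sxx), and the critical t value is about 2.00.

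- Urban 10 falling 50%, rural 4 flat: slope = −5/65 = −0.0769; mean = 7.5 + 4 = 11.5; SE = √(11.5/23,952.5) = 0.0219; ratio 3.51; Φ(3.51 − 2.00) = 0.93.
- Urban 1 falling 50%, rural 0.5 flat: slope = −0.5/65 = −0.00769; mean = 0.75 + 0.5 = 1.25; SE = 0.00722; ratio 1.06; Φ(1.06 − 2.00) = 0.17. Total cases are 66 × 1.25 = 82.5, near the 100-chart scale.

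**Simulation when Hypothesis 1 is false** (a fall means significant and negative; the correlation uses the five full years, pooled)

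| Assumed scenario | Combined slope falls | Combined falls, interaction not significant | Annual correlation falls | Both site slopes fall |
|---|---|---|---|---|
| Urban 10 (−50%), rural 4 flat | 94% | 6% | 53% | 3% |
| Urban 10 (−50%), rural 4 (+20%) | 83% | 1% | 40% | 0.2% |
| Urban 1 (−50%), rural 0.5 flat | 17% | 13% | 9% | 0.6% |

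In the last row, 12.8% of runs had a combined fall with no significant interaction: 12.8/17 is about three-quarters of the combined positives. A separate set of assumptions gives the same pattern. With 100 cases split 50/50, an urban-only 80% fall and rural flat, the combined slope falls in 47.5% of runs, 24.7% are unflagged, and both site slopes fall in 1.9%. With 250 cases per setting, 1.0% are unflagged.

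**When both settings do fall by 50%**

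- From 10 and 5 per month: both site slopes are significant in 86% of runs. The interaction is also significant in 43%, because equal percentage falls are unequal falls in counts.
- From 1 and 0.5 per month: urban ratio = 0.00769/√(0.75/23,952.5) = 1.37, power Φ(1.37 − 2.00) = 0.27; rural ratio = 0.00385/√(0.375/23,952.5) = 0.97, power Φ(0.97 − 2.00) = 0.15; jointly 0.27 × 0.15 = 0.04. The combined slope has 38%.

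**The location main effect.** The text adds only an interaction to the month-only model. Taken literally, both sites share an intercept and the slopes absorb the difference in volume. With urban 10 and rural 4, both flat, the rural slope then came out significantly negative in 99.8% of runs.

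**The case against.** A reader might infer that the protocol will report an urban-only fall as a fall in both. The documents do not support that. There is no rule that reads a combined trend as holding in each setting, so the accurate word is could.

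The strongest defence is that the safeguard is already planned. A location-by-month model with its main effect contains both site slopes, and its interaction is significant in about 93% and 98% of runs in the two high-volume scenarios. The 94% and 83% figures therefore describe a reader who ignores a planned analysis. This stands at high volumes. It is weaker near 100 charts, and a significant interaction still does not say which setting falls, or whether either does.

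Other points on that side:

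- Pooling in the annual correlation is the natural reading but is not stated, and that analysis is labelled an alternative.
- A main effect is conventionally fitted with an interaction and may be intended.
- The objective is to describe trends, so a pass-or-fail rule on both slopes is not the only acceptable analysis. This stands, and it shapes the fix.
- Such detail may sit in a statistical analysis plan that is not shown. However, the protocol itself chose these tests and tied them to Hypothesis 1.

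**Conclusion.** The point holds as a mismatch between hypothesis and test. Hypothesis 1 concerns both settings, and the protocol does not base its conclusion on each setting's slope. The possible error is large if the combined slope is read alone (about 94% in the first scenario). If the interaction is fitted with a main effect and heeded, it is small at high volumes (about 6% and 1% unflagged) and still material near 100 charts (about 13% of runs).

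These sizes rest on assumed volumes, splits, linear changes and Poisson variation. The mismatch itself rests only on the text. It should be corrected, because the change is cheap and determines what can be concluded about the rural setting.

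**What to change.** In Study Statistics, under Hypothesis 1:

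1. Fit the site-month counts (66 months × 2 sites = 132 rows) with location, month and location-by-month, naming the location main effect.
2. Judge Hypothesis 1 on the rural slope and the urban slope, each reported with a 95% CI.
3. Claim a decrease only for a setting whose own interval lies wholly below zero, and in both only if both intervals do. Requiring both needs no multiplicity correction for the joint claim.
4. Use the interaction only to compare the two trends.
5. Compute the annual correlation separately for each hospital.

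The cost is a few sentences and one re-specified model on the same data. The downside is lower power to claim a fall in both: slight at high volumes (86% at 10 and 5 per month) but severe near 100 charts (about 4%, against 38% for the combined slope). At that scale the two slopes and their intervals should be reported descriptively.

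### The rural-urban trend interaction is tested on absolute monthly counts, so hospitals of unequal volume can show different trends when their percentage declines are equal

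*Protocol*

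**What the plan says.** The Objectives section words Hypothesis 1 as a fall in numbers: "The number of diagnosed TB cases initiating therapy in rural and urban settings will decrease over time". Under Study Statistics (retrospective study and historic cohort study), the test is ordinary linear regression: "we will fit a linear regression model with number of monthly cases diagnosed as outcome and study period (in months) as the predictor". Months run from 1 to 66. The site comparison follows: "We will further fit an interaction term in this regression model, between dichotomous TB diagnosis location (urban or rural) and continuous study period". The alternative analysis is a Pearson correlation of annual counts with year. No count model, log link, offset, denominator or robust variance is named.

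The protocol describes the number of charts in two ways. Study Procedures sets a quota: "the abstractor will look for an alternative case until the 100-patient sample is reached". Study Statistics says: "We will assess all available charts of pediatric patients admitted with active TB". The retrospective cases are those "diagnosed with TB at either Mulago National Referral Hospital or a Fort Portal Regional Referral Hospital in Uganda", with no stated split between the two hospitals. The size of the expected decline is not given. The sample size calculations "are based on Hypothesis 2 using the t-statistic", that is, on length of stay, and no power figure is given for the trend model.

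**The concern.** A linear model of counts measures trend in cases per month. If a busy and a less busy hospital both lose half their cases, the busy one loses more cases per month. The month-by-location term then differs from zero although the relative trends are identical. One site is a national referral hospital and the other a regional one, so equal volumes cannot be taken for granted.

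The abstract says the results should improve understanding of rural healthcare disparities. A significant interaction would naturally be read as a disparity in trend, when it may show only that one hospital is larger.

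There is a second effect. The interaction model uses one residual variance for both sites, but the variance of a count rises with its mean. The busier site inflates the standard error used for the quieter site's slope.

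**Working it through.** **The plan's own power figure.** The only one is for length of stay: more than 80% power for 16 days with n = 100. From the quoted IQR of 21-60 days, assuming normality, SD = (60 - 21)/1.349 = 28.9. At 50:50, SE = 28.9 × √(1/50 + 1/50) = 5.78, 16/5.78 = 2.77, and power = Φ(2.77 - 1.96) = 79%. The figure is reproduced to within about a point. It says nothing about Hypothesis 1.

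**Inputs for the trend model.** From the protocol: 66 months, two sites and hence 132 site-months, 100 charts under the quota. Assumed: the split, the decline (same percentage at both sites, month 66 relative to month 1), Poisson counts, two-sided 5% tests, and a model containing site, month and month-by-site.

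**Sparseness.** 100/132 = 0.76 cases per site-month. At equal volumes the expected share of zero cells is exp(-0.758) = 47%; at 80:20 it is about 52%.

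**Interaction by hand: 80:20, cases halve.**
- Mean counts per month: 80/66 = 1.21 and 20/66 = 0.30.
- A halving at the busier site runs from about 1.68 to 0.84 per month, and at the quieter site from 0.42 to 0.21. The fitted linear slopes are about -0.0128 and -0.0032, a 4:1 ratio that merely repeats the volume ratio.
- Sum of squares of month: 66 × (66² - 1)/12 = 23,952.5.
- Pooled residual variance: about (1.21 + 0.30)/2 = 0.758.
- SE of the slope difference: √(2 × 0.758/23,952.5) = 0.00795.
- z = (0.0128 - 0.0032)/0.00795 = 1.21, so rejection is about Φ(1.21 - 1.96) = 23%.

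Simulation agrees. Rejection of the interaction with about 100 charts and the same percentage decline at both sites:

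| Split | Falls to 1/2 | Falls to 1/4 |
|---|---|---|
| 50:50 | 5-6% | 5-6% |
| 60:40 | 7% | 13% |
| 70:30 | 13% | 34-35% |
| 80:20 | 22-23% | 64-65% |
| 90:10 | 36% | 88% |

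The Poisson log-link model stays at about 4-6%. With no trend, or with equal absolute slopes (checked at 70:30 and 80:20), linear regression holds 5%. Robust (HC3) errors do not help (80:20: 21% and 61%), so the cause is the additive scale and not unequal variance.

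**All-available-charts reading.** z grows with the square root of the number of charts. At 80:20 with halving, 600 charts give z = 1.21 × √6 = 2.96 and rejection of about 84% (simulated: 83%). Simulation gives 56% for 300 charts and 97% for 1,000. These totals are assumed.

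**Slope at the smaller site: 80:20.** The SE that the model uses is √(0.758/23,952.5) = 0.00562; the true SE is √(0.303/23,952.5) = 0.00356. The effective critical value is 1.96 × 0.00562/0.00356 = 3.10, so the lower-tail size is about 0.1% (0.1-0.2% in simulation) instead of 2.5%. Simulated power is 2% and 10% for a fall to a half and to a quarter, against 14% and 40-41% for Poisson. A separate linear fit for that site gives 15% and 42%.

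**The case against.** The strongest objection is that Hypothesis 1 is about the number of cases. On that scale a larger absolute fall at the busier hospital is a true difference, and linear regression tests it at the correct 5%. This stands. A reader might infer that the planned interaction is false in every sense, or significant by construction. The documents support neither: the result misleads only when read as a difference in relative trend, and at about 100 charts it is far from certain even at 80:20.

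The split is also unknown. The length-of-stay power claim fits near-equal groups: at 80:20 the same inputs give SE = 28.9 × √(1/80 + 1/20) = 7.2 and power of about 60%. At 50:50 there is no inflation, and at 60:40 it is small. This stands too, but the protocol fixes no split, and a calculation for length of stay does not make the monthly volumes equal.

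A reader might further infer that linear regression is why the smaller site has little power. It is not: a separate linear fit matches Poisson. The loss comes from few cases and from the shared variance, and the protocol does not say that the rural slope will be tested inside the interaction model. Nor does sparseness cause the misleading interaction; more charts make it worse.

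Finally, the objective is to describe trends, the hypothesis is a fall in both settings, and the interaction is a further step. That limits how much rests on it. Still, it is the only planned formal comparison of the two trends.

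**Conclusion.** The concern holds in a limited form. The protocol fixes an interaction on the absolute scale. If volumes differ and cases really decline, it can flag different trends where the percentage declines are equal. With about 100 charts the rate ranges from the nominal 5-6% at 50:50 to 22-23% (cases halve) or 64-65% (cases fall to a quarter) at 80:20; it is higher at 90:10 or with more charts. These figures rest on assumed splits, assumed equal percentage declines and Poisson variation. Overdispersed counts lower them (negative binomial, 80:20: 16% and 45%).

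The smaller-site slope test inside the interaction model is too conservative when volumes differ. Neither a count model nor separate fits make 100 charts adequate for that slope at 80:20.

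The analysis is not invalid as a test of absolute slopes. It should be changed because a rural-urban comparison of trend ought not to depend on hospital size, and the change is cheap.

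**What to change.** First reconcile the 100-chart quota in Study Procedures with the all-available-charts statement in Study Statistics. If charts are picked until a quota is filled, the monthly counts partly reflect the picking, and no model repairs that. The trend analysis needs the complete count of eligible cases per site and month.

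Then replace the linear model for Hypothesis 1 with a Poisson log-link model of the 132 site-month counts, using quasi-Poisson or negative binomial errors if the counts are overdispersed. Name all three terms: site, month and month-by-site. The present text names only the interaction. A site main effect is conventional and probably intended, but if it were left out, the linear interaction would be significant in 94% (70:30) to 100% (80:20) of datasets with no trend at all.

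Report the annual percent change per site with its 95% CI, and the ratio of the two rates of change. Absolute changes in cases per month may be given descriptively.

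The model change costs a sentence or two of wording, uses standard software and by itself needs no further data. The downside is that effects are expressed as percent change instead of cases per month. If the reconciliation leads to counting all eligible cases, that adds record review beyond 100 charts.
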